## Randomization

After signing informed consent and undergoing baseline assessment of primary and secondary outcome measures, eligible participants will be assigned 1:1 randomly via computer to one of two 12-week, 3×/week, 1-h interventions: (1) aerobic exercise intervention (AE) or (2) a stretching and toning control intervention (ST). Participants will receive intervention assignment via a secure telephone call.

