### Sample size calculations

A power analysis was considered for determining sample size. However, a power analysis was ultimately determined not to be appropriate for the current trial due to the lack of direct data on the relationship between aerobic exercise and reduction in suicide risk. Additionally, recruitment and sample size for this protocol is associated with the ongoing parent R01-funded protocol.

The sample size for the parent R01-funded study is 200 outpatient individuals with SZ. This sample size was determined based on a focus on cognition as the primary outcome, specifically the MCCB total composite score. Prior literature suggests average scores of individuals with SZ fall between 1 and 2.5 standard deviations lower than MCCB averages. Therefore, a 0.50 standard deviation was chosen as a meaningful target effect size for powering the trial. The pilot for the parent study found a large effect size for the AE intervention group compared to controls suggesting a 0.893 standard deviation improvement in the intervention group compared to controls. The parent study sample size calculations assumed a loss-to-follow-up rate of 20% with 80 participants remaining in each arm (100 × 0.8). According to these calculations, the parent study is powered to detect moderate or larger effect size difference with > 80% power. The current study retains confidence that the sample size will provide adequate power to detect a clinically meaningful effect size for suicide risk as the primary outcome.

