### Data analyses

All primary analyses will be carried out on an intent-to-treat (ITT) basis, i.e., all subjects randomized will be analyzed according to the treatment they were assigned regardless of adherence to treatment. Level of fidelity to training intensity, accounting for adherence, will be controlled for in these analyses. All statistical tests will be two-sided with critical value α = 5%.

Mixed effects regression will be used to model suicide risk as a function of time (0, 6, 12 weeks), treatment group (AE or ST), interaction of time by treatment group, and site (1, 2, 3, or 4). The efficacy of AE to improve suicide risk in people with SZ will be represented by the statistical significance of the time by treatment group interaction. The effect of AE on mood, sleep, and executive functions will be tested by conducting similar analyses, i.e., mixed effects regression across 0, 6, and 12 weeks.

Mediators in the relationship between AE and suicide risk will be identified by multi-step process. A mediation effect will be estimated by taking the expected value of the total effect of AE on changes in suicide risk and subtracting the effect when changes in mood, sleep, and executive functioning have been controlled. These mediation effects will be tested by fitting a Structural Equation Model (SEM) with change in depressed mood, sleep, and executive function from baseline to 6 weeks as mediators of the relationship between AE treatment and change in suicide risk from baseline to 6 weeks as well as later changes in suicide risk from 6 to 12 weeks using MPlus version 8. The mediator-outcome relationship can be confounded by other time-varying covariates (e.g., BMI changes), and these will also be adjusted for in the model.

Change in suicide risk from baseline will be modeled using mixed effect regression predicted by contemporaneous change in aerobic fitness from baseline as measured by VO_2_max tests (at 6 and 12 weeks), controlling for treatment group and other covariates. The ability of aerobic fitness improvement to predict reduction in suicide risk will be represented by a statistically significant positive regression coefficient for change in aerobic fitness.

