Demographic and other biologically relevant baseline variables (e.g., sex, depression, and smoking status) will be included as control variables if there is evidence of randomization imbalance in them. Multiple imputation will be used to handle missing data using the MI and MIANALYZE SAS procedures.

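### Baseline covariates enter only on evidence of chance imbalance, so the efficacy model is chosen by relation to arm, not prognosis, and stays unfixed until arms are compared at baseline

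*Protocol article*

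**What the plan says.** Under Data analyses, the primary model for suicide risk is a mixed effects regression over weeks 0, 6 and 12. Its terms are time, "treatment group (AE or ST), interaction of time by treatment group, and site (1, 2, 3, or 4"). Efficacy "will be represented by the statistical significance of the time by treatment group interaction". Week 0 is therefore one of the modelled outcome times, and site is in the model whatever the data show. Training fidelity is also unconditional: "Level of fidelity to training intensity, accounting for adherence, will be controlled for in these analyses".

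Further baseline variables are handled differently. The candidates are described as "Demographic and other biologically relevant baseline variables (e.g., sex, depression, and smoking status"), and they "will be included as control variables if there is evidence of randomization imbalance in them".

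Under Randomization, "eligible participants will be assigned 1:1 randomly via computer". The Background lists depression, disturbed sleep, weaker cognition and greater symptom severity among the predictors of completed suicide in this population. Under Baseline measures, the BDI, PSQI and PANSS are all collected before allocation.

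**The concern.** A covariate is worth adjusting for because it predicts the outcome. Evidence of imbalance shows only how it happens to fall across arms, and after computer randomisation that is chance. Under this rule baseline depression, which the article's own Background treats as a predictor, is left out if the arms look alike on it. A variable unrelated to suicide risk goes in if the arms happen to differ.

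Two things are at stake. The efficacy model is not known until someone has compared the arms at baseline, and the same rule carries over to the parallel analyses of mood, sleep and executive function, which could end with different covariate sets. In addition, any power available from a truly prognostic covariate is collected only by accident.

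**Working it through.** **1. The article's own figure.** The only power statement is for the parent study's cognition outcome (Sample size calculations): "a 0.50 standard deviation was chosen as a meaningful target effect size for powering the trial", with 100 × 0.8 = 80 per arm after loss. Two-sided 5%, normal approximation: 0.50 × √(80/2) = 3.162; 3.162 − 1.960 = 1.202; Φ(1.202) = 0.885. This agrees with the stated power above 80%. It does not depend on the covariate rule.

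**2. How often the trigger fires under perfect randomisation.** For k independent covariates screened at level a, P(at least one enters) = 1 − (1 − a)^k. The article names three variables as examples. The other values of k and both screening levels are assumptions.

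| k | a = 0.05 | a = 0.10 |
|---|---|---|
| 3 | 1 − 0.95³ = 14% | 1 − 0.90³ = 27% |
| 5 | 1 − 0.95⁵ = 23% | 1 − 0.90⁵ = 41% |
| 10 | 1 − 0.95¹⁰ = 40% | 1 − 0.90¹⁰ = 65% |

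**3. Does a baseline main effect sharpen the stated test?** Write the outcome of person i at time t as (time, group and time-by-group terms) + site + βx_i + random intercept + error. In the change from week 0 to week 12, site, βx_i and the intercept all cancel, and the time-by-group contrast rests on that change. In 60 simulated trials of the stated model (80 per arm, x correlated 0.5 with the outcome), the week-12 interaction had these mean standard errors:

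- complete data: 0.1413 without x and 0.1413 with x, with identical estimates;
- 20% missing at week 12: 0.1538 without x and 0.1533 with x.

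**4. When power is lost.** Simulation of 6,000 trials per scenario. Assumptions: 80 per arm, correlation 0.6 between repeated outcomes, x correlated 0.5 with the baseline outcome, true effect 0.4 SD, trigger at p<0.05. The change analysis stands for the time-by-group test. Including x there corresponds to a covariate-by-time term.

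| Scenario | Analysis | Never adjusted | Triggered | Always adjusted |
|---|---|---|---|---|
| x predicts level only | change | 0.799 | 0.798 | 0.795 |
| x predicts level only | ANCOVA | 0.880 | 0.883 | 0.907 |
| x also predicts change (assumed slope 0.3) | change | 0.755 | 0.761 | 0.800 |
| x also predicts change (assumed slope 0.3) | ANCOVA | 0.780 | 0.793 | 0.897 |

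A hand check of the change rows. With level only, the variance of change is 2 × (1 − 0.6) = 0.80, the SE is √(0.80 × 2/80) = 0.141, and power is Φ(0.4/0.1414 − 1.96) = 0.81. With slope 0.3 and x ignored, the variance is 0.80 + 0.3² = 0.89, the SE is 0.149, and power is 0.76. Both are close to the simulation. In this assumed case x explains 0.09/0.89 = 10% of the variance of change.

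**5. Type I error under the trigger.** With no true effect, rejection rates were 0.044 to 0.052 in the change and ANCOVA analyses. In an analysis of the final value alone the rate fell as low as 0.036, which is conservative. Simulation error near 0.05 is about √(0.05 × 0.95/6000) = 0.003.

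**The case against.** The strongest reply is that the rule does little harm in this particular model. Site is always included, week-0 suicide risk is already used as an outcome, and the test is a within-person contrast that a baseline main effect cannot sharpen. That stands, and it rules out some stronger readings.

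- A reader might apply the usual 1 − r² factor, take r = 0.3 to 0.5, and infer that 9% to 25% of the residual variance is being thrown away. That formula belongs to a single-endpoint or ANCOVA-type analysis. The article specifies neither and gives no correlation.
- A reader might infer that selecting covariates after inspection invalidates the standard errors. Step 5 shows no inflation when the trigger is applied mechanically.
- A reader might infer that all covariates are conditional. Site and training fidelity are not.
- A reader might count the illustrative list and the absent threshold as faults in themselves. An analysis plan that is not shown may supply both, so they are not the finding. For the same reason the percentages in step 2 are illustrations: the article does not say that imbalance will be judged by a significance test.

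What the reply does not remove is the trigger. A threshold or a closed list would make the rule reproducible, but covariates would still be chosen by accident of allocation rather than by prognosis.

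**Conclusion.** The point holds as a weakness of model specification. The article states a rule that ties adjustment to chance imbalance and leaves the efficacy model open until baseline data are inspected by arm, although it identifies prognostic variables and collects them before allocation. Under the assumptions of step 2, at least one covariate enters by chance in 14% of trials with three candidates and 40% with ten.

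The consequence for the primary test is modest. Type I error is not inflated, and nothing is lost if the covariates predict only the level of suicide risk. If a covariate predicts change, the illustrative loss is 0.761 against 0.800 in the change analysis and 0.793 against 0.897 in an ANCOVA. Those figures rest on an assumed slope and assumed correlations. The Background's predictors concern completed suicide, and the article does not show that they predict 12-week change in C-SSRS. The change is worth making because it is cheap and because this study has no power calculation of its own for suicide risk.

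**What to change.** Replace the trigger with a short list of prognostic baseline covariates, fixed before any data are seen by arm and always included: for example baseline BDI, sex and smoking status, with site retained. State how they enter, because main effects alone leave the efficacy test as it is. There are two workable forms:

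- keep weeks 0, 6 and 12 as outcomes and add covariate-by-time terms; or
- model the 6- and 12-week outcomes with baseline C-SSRS as a covariate, plus the listed variables.

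Do not use baseline C-SSRS as a covariate while week 0 is also an outcome. By the same logic, baseline BDI should not be a covariate in an analysis where week-0 BDI is an outcome.

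Show baseline balance descriptively. If adjustment triggered by imbalance is kept at all, make it a sensitivity analysis.

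The cost is a rewritten sentence or two, a few degrees of freedom and a slightly larger model. The example covariates are already collected at baseline.

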### Confidentiality and data management

All study documents will be deidentified and labeled using participant identification codes. The identification code key, contact information, consent forms, and medical documents with personal health information will be kept confidential. Hard copies are kept in secure, locked cabinets. Electronic copies will be stored in password-protected computers. Only IRB authorized individuals will be able to access study data.

## Discussion

Individuals with SZ are at an elevated risk for committing and completing suicide [1–3]. Current pharmacological and psychotherapeutic treatment approaches provide limited benefits to ameliorate suicide risk in this population. Aerobic exercise may help mitigate many of the predictors of suicide risk. Therefore, engaging individuals with SZ in AE may be a beneficial treatment approach.

### Trial status

This trial (protocol version 1.7, January 4, 2020) is currently active. Recruitment of participants for the parent study started in May of 2018. Recruitment for the Suicide Reduction in Schizophrenia via Exercise amendment started in November of 2019. Recruitment of participants is scheduled to be completed July 31, 2021.

## Data Availability

Anonymized data from the study will be available from the author after the trial has ended.

## Abbreviations

ACSM: American College of Sports Medicine
AE: Aerobic exercise
AF: Aerobic fitness
BAI: Beck Anxiety Index
BDI: Beck Depression Index
BDNF: Brain-derived neurotrophic factor
BHS: Beck Hopelessness Scale
BSS: Beck Suicide Ideation Scale
BMI: Body mass index
CBTs: Cognitive behavioral therapy for suicide
C-SSRS: Columbia Suicide Severity Rating Scale
CTQ: Childhood Trauma Questionnaire
DSM: Diagnostic and Statistical Manual of Mental Disorders
DSMB: Data Safety and Monitoring Board
ERQ: Emotion Regulation Questionnaire
FTND: Fagerström Test for Nicotine Dependence
HR: Heart rate
ICE: Improving Cognition via Exercise
IPAQ: International Physical Activity Questionnaire
IRB: Institutional Review Board
ISST: The InterSePT Scale for Suicidal Thinking
ITT: Intent-to-treat
MCCB: MATRICS Consensus Cognitive Battery
NIMH: National Institute of Mental Health
PANSS: Positive and Negative Symptom Scale
PRN: Pro re nata (“as needed”)
PSQI: Pittsburgh Sleep Quality Index
RCT: Randomized clinical trial
RFL: Reasons for Living Inventory
SAE: Serious adverse event
SCID: Structured Clinical Interview for DSM-V Axis 1 Disorders
SCORS: Schizophrenia Cognition Rating Scale
SEM: Structural Equation Model
SLOF: Specific Levels of Functioning scale
SMI: Serious mental illness
SSRI: Serotonin reuptake inhibitors
ST: Stretching and toning
SWL: Satisfaction with Life Questionnaire
SZ: Schizophrenia
TAS-20: Toronto Alexithymia Scale
UPSA: UCSD Performance-based Skills Assessment
